#### 2.4.2. Components of the Intervention

The intervention comprises two core dimensions: (1) Collaborative agenda, and (2) Training. The collaborative scheduling component is co-designed with participants to improve and apply planning, organizational, and time management skills in daily life. It is intended for daily use to establish a routine of planning and monitoring activity completion. In parallel, each participant will complete twelve 45-min virtual training sessions, delivered twice per week across six weeks. Training activities are gamified to enhance motivation while targeting planning, organization, time management, and emotional self-regulation.

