#### 2.4.4. Delivery Format and Dosage

The program will be delivered entirely in a digital, remote format over six weeks. Participants will engage in scheduled online training activities, utilize the digital agenda for planning and organization, and attend synchronous videoconference sessions led by trained occupational therapists. The six-week protocol comprises 12 child/adolescent sessions (two per week) and six parent/teacher sessions (one per week), aligning with the dosage planned for the subsequent randomized controlled trial. In addition to scheduled sessions, participants will be instructed to use the collaborative agenda daily (seven days per week) throughout the intervention to support continuous engagement and transfer of strategies to natural home–school contexts.

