#### 2.4.8. Participant Support and Supervision

Throughout the intervention, participants will have the support of an assigned therapist from the research team, available to address questions or issues via the application’s internal chat or email (for children/adolescents and legal guardians). In addition, two supervisory videoconferences will be scheduled—Week 1 and Week 3—to answer questions and assess progress. If necessary, users or guardians may request additional videoconferences via chat or email, which will be scheduled according to the availability of the research team and families.

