#### 2.9.2. Feasibility Outcomes

The primary aim of this study is to assess feasibility across multiple domains, following established frameworks for pilot and feasibility trials [52,67,68]. Progression criteria for feasibility outcomes are summarized in Table 3 and Figure 2.

The following outcomes will be evaluated:

*Recruitment and Retention*

Recruitment will be measured as the proportion of eligible participants who consent to participate, and the average recruitment rate per month. Retention will be defined as the percentage of participants who complete all planned assessments at T1 (post-intervention) and T2 (follow-up).

*Data Completeness and Missing Data*

Data completeness will be calculated as the proportion of participants providing valid data for each measure at each time point. Patterns and reasons for missing data will be documented. This information will inform the feasibility of data collection procedures and guide refinements for a future trial. Primary feasibility analyses will use complete cases. Sensitivity analyses using multiple imputation may be performed for exploratory clinical outcomes, but the results will be interpreted with caution given the small sample size.

*Adherence*

Adherence will be assessed based on three components:(a)use of the digital agenda on at least 80% of intervention days (over 6 weeks),(b)completion of at least 80% of scheduled online training activities, and(c)attendance at 100% of planned videoconference sessions.

Adherence will be reported as the proportion of participants meeting these criteria.

*Intervention Fidelity*

Fidelity will be ensured through a structured process: all occupational therapists delivering the intervention will complete a 20-h training course prior to implementation, covering theoretical foundations, intervention procedures, and use of digital tools. Fidelity will be monitored using session checklists, regular supervision meetings, and ongoing remote support. Fidelity will be categorized as high (≥80% of protocol elements delivered), moderate (60–79%), or low (<60%).

*Acceptability and Usability*

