In contrast to the assumption that family involvement in DiverAcción is primarily psychoeducational, the protocol incorporates active family mediation and routine-based practice throughout the intervention period. Parents are required to support regular use of the platform and the collaborative agenda, establish consistent daily routines (e.g., homework, personal care, organization of materials), and apply executive and self-regulation strategies in the home context. These aspects are explicitly addressed during scheduled videoconference sessions with parents, where goal setting, supervision strategies, environmental structuring, and family stress management are discussed and adapted as needed. Importantly, family-mediated change is not only encouraged but also monitored through a multi-informant assessment strategy, including parent-, teacher-, and self-reported measures of executive functioning, emotional regulation, time management, parental stress, and perceived parental competence. This approach allows indirect monitoring of family-level and contextual changes over time.

Nevertheless, DiverAcción differs from highly manualized programs such as Cog-Fun and POET in that family-mediated practice is embedded within a flexible, digitally supported framework rather than prescribed through standardized homework protocols with formal fidelity checklists. This distinction should be considered when interpreting generalization processes and highlights an area for further refinement in future controlled trials.

A notable difference from Teen Cog-Fun is the intensity of family involvement. Whereas Teen Cog-Fun includes only two sessions for parents, DiverAcción provides six dedicated sessions (within an eight-session structure) for parents and teachers. It is reasonable to assume that two sessions may not be sufficient to address the substantial parental challenges of raising an adolescent with ADHD, as suggested by Theule et al. [76], who reported lower satisfaction regarding parents’ own achievements in parental self-efficacy. This expanded involvement in DiverAcción aims to strengthen parental competence and reduce stress through ongoing guidance and interactive support mechanisms.

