**Figure 3 healthcare-14-00323-f003:**
[figure not shown]
CONSORT Flow Diagram Adapted for Feasibility Trials. It will be completed after the collection.

**Table 1 healthcare-14-00323-t001:** DiverAcción Program Structure by Target Group.

Dimension	Frequency	Main Aim	Description	Administered To
Collaborative Agenda	Daily (7 days/week)	Promote planning and monitoring in natural contexts	Participants co-design a personal agenda to schedule daily activities, prioritize tasks, estimate duration, and monitor completion.	Children/Adolescents
Training Sessions	12 sessions (2/week, 45 min each, 6 weeks)	Develop executive skills and emotional regulation through gamified tasks	Virtual sessions focused on planning, organization, time management, and emotional self-regulation using interactive exercises.	Children/Adolescents
Psychoeducation Sessions	6 sessions (1/week, 45 min each, 6 weeks)	Support generalization and caregiver mediation	Sessions for parents and teachers to reinforce strategies, manage routines, and reduce stress.	Parents/Teachers
Therapeutic Support	Continuous (chat/email) + 2 videoconferences (weeks 1 and 3)	Provide guidance and resolve doubts	Integrated communication tools and scheduled videoconferences to monitor progress and address questions.	Children/Adolescents & Parents/Teachers

**Table 2 healthcare-14-00323-t002:** Variables, instruments and timing of administration.

Variables	Instruments	Time Data Collection	Administered to:
Previous experience with digital interventions, sociodemographic, educational and economic data of children and adolescents, pharmacological treatment, other behavioral or psychoeducational interventions	interview	T0	Parents
Preferences regarding digital intervention format	interview	T0	Children and Adolescents
Symptom severity in inattention, hyperactivity–impulsivity and oppositional behaviors (not for subtype classification)	SNAP-IV	T0	Parents
Therapeutic attitudes of professionals towards technology	e-TAP-T	T0	Teachers Occupational therapists
IQ estimated	WASI-II	T0	Children and Adolescents
Feasibility	Automated metrics recorded by the platform: adherence, number of uses, sessions, time of use, errors	T1	Children and Adolescents Parents Teacher Occupational Therapists
Acceptability	TAM questionnaire	T1	Children and Adolescents Parents Teacher Occupational Therapists
Usability	SUS	T1	Children and Adolescents Parents Teacher Occupational Therapists

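### No visible adherence or progression criterion sets a threshold for attending the six weekly parent/teacher sessions, so the adherence domain can return GO with none of them attended

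*Protocol article*

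**What the plan says.** Section 2.4.4 sets the programme at 12 child sessions and "six parent/teacher sessions (one per week), aligning with the dosage planned for the subsequent randomized controlled trial". Section 2.4.6 gives the reason for the caregiver part: carrying the child's strategies over into daily routines. Table 1 lists psychoeducation as a dimension of its own, "6 sessions (1/week, 45 min each, 6 weeks"), although section 2.4.2 says "The intervention comprises two core dimensions: (1) Collaborative agenda, and (2) Training".

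Adherence in section 2.9.2 has three components: (a) agenda use on at least 80% of days, (b) at least 80% of training activities, and (c) "attendance at 100% of planned videoconference sessions". The Adherence row of Table 3 repeats these three for GO. Its AMEND and STOP cells mention agenda and training only.

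On the number of videoconferences, section 2.4.8 says "two supervisory videoconferences will be scheduled—Week 1 and Week 3". Table 1 has them only in the Therapeutic Support row, apart from psychoeducation: "Continuous (chat/email) + 2 videoconferences (weeks 1 and 3"). The Abstract and one paragraph of the Discussion also give two. Another paragraph of the Discussion describes parent sessions held by videoconference and "six dedicated sessions (within an eight-session structure) for parents and teachers". Section 2.4.4 mentions therapist-led videoconference sessions without a number.

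**The concern.** The study exists to decide whether to go on to a randomised trial of this package. The caregiver sessions belong to that package, and whether parents and teachers will come to them is a basic feasibility question. Table 1 assigns the agenda and training to the children and adolescents only, so components (a) and (b) say nothing about caregivers. If (c) covers only the two support calls, no adherence threshold touches the six sessions, and an adherence GO would carry an untested component into the trial. If (c) is read more widely, the same data can give the opposite result. A denominator chosen after the data are seen would defeat the purpose of progression criteria fixed in advance.

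**Working it through.** There is no stated figure to reproduce. The check takes a family with full agenda use, full training and both support calls, and varies only attendance at the six psychoeducation sessions.

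**Inputs.** Training sessions 12, psychoeducation sessions 6, scheduled support videoconferences 2 (Table 1; sections 2.4.4 and 2.4.8). Scheduled contacts: 12 + 6 + 2 = 20. Psychoeducation is 6/20 = 30% of them.

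**Adherence with 0 of 6 attended.**
- Components (a) and (b): unaffected.
- Component (c), two videoconferences: 2/2 = 100%, GO condition met.
- Component (c), eight contacts (6 + 2): 2/8 = 25%, GO condition not met.

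**Fidelity.** Table 3 bands: GO at 80% or more, AMEND 60–79%, STOP below 60%. The protocol elements are not listed, so assume one element per session and count a missed session as not delivered.

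| Denominator | 0 of 6 held | Most that can be missed with GO |
|---|---|---|
| Only sessions that took place | 14/14 = 100%, GO | all 6 |
| All 20 contacts | 14/20 = 70%, AMEND | 4 of 6 (16/20 = 80%) |
| Training and psychoeducation only, 18 | 12/18 = 67%, AMEND | 3 of 6 (15/18 = 83%; a fourth gives 14/18 = 78%) |

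**Other domains.** Recruitment, retention, data completeness, acceptability, usability and dropout do not measure session attendance. Table 2 lists platform metrics, among them adherence and sessions, for parents and teachers as well as children, but attaches no threshold to them.

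**Level for a new item.** 80% of 6 = 4.8, so at least 5 sessions (5/6 = 83%); 4/6 = 67% falls short.

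**The case against.** Four points on the other side have weight.

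- **The sessions are not wholly unmeasured.** Table 2 plans platform session metrics for parents and teachers. A reader might infer that caregiver participation goes unrecorded; the documents do not support that. What is missing is a threshold that feeds the decision.
- **Fidelity may act as a backstop.** Clinicians complete a checklist after each session, and fidelity has its own GO/AMEND/STOP bands. If undelivered sessions count as elements, complete non-delivery gives AMEND. This stands, but only in part: the elements are not listed, the measure concerns delivery rather than who came, and 3 or 4 of the 6 sessions could be missed with fidelity still at GO.
- **The two readings of (c) are not equally likely.** A reader might infer that two and eight contacts are on a par. They are not: the Abstract, section 2.4.8, Table 1 and part of the Discussion agree on two, and eight rests mainly on loose Discussion wording. The main defect is therefore the missing threshold; the blurred denominator comes second.
- **Figure 2 is not shown.** Section 2.9.2 cites it with Table 3 for the progression criteria, so an attendance criterion there cannot be ruled out.

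It would also go too far to say that a parent and a teacher must both attend every week. No section says so.

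**Conclusion.** The point holds in this form: the six sessions are part of the dose planned for the randomised trial, and no visible adherence or progression criterion sets a threshold for attending them. On the plain reading, adherence GO is compatible with 0 of 6 attended; on the Discussion's wider wording the same record falls from 100% to 25% on component (c).

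A reader might infer that the study as a whole would certainly return GO with the component unattended. The documents do not support that, since fidelity could fall to 70% or 67% if unheld sessions enter its denominator. The fidelity figures rest on the assumption of one element per session. This cannot be left to an unseen analysis plan, because the article itself fixes the adherence components and the progression table. The change should be made; confidence is medium because of Figure 2.

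**What to change.** In section 2.9.2 and the Adherence row of Table 3:

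1. State that component (c) means the two supervisory videoconferences of weeks 1 and 3, and say who must attend. Reconcile section 2.4.4, section 2.4.8 and the Discussion with Table 1 on this count.
2. Add attendance at the psychoeducation sessions as a fourth adherence item. Require the plan's existing level of at least 80%, that is at least 5 of 6, for GO, and let a shortfall lead to AMEND.
3. Report parent and teacher attendance separately and descriptively. Do not add a separate STOP rule for teachers: whether low teacher attendance alone should halt progression is for the sponsor to decide, and nothing in the article calls for it.

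The cost is small. Attendance has to be logged, for which a field on the existing session checklist should be enough, and GO becomes somewhat harder to reach. Neither the programme nor its dose changes.

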#### 2.9.3. Exploratory Clinical Analyses

Exploratory analyses of clinical outcomes will aim to estimate variability and preliminary trends, not to draw confirmatory conclusions. Where appropriate, repeated-measures ANOVA or the nonparametric Friedman test will be used to compare results at different time points, prioritizing effect sizes and confidence intervals over *p*-values. Bonferroni-corrected post-hoc analyses will be performed for exploratory purposes only. Statistical significance will be set at *p* < 0.05 for these tests, but interpretation will be cautious. All analyses will be performed using IBM SPSS Statistics v28.

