## 2. Methods

### 2.1. Design

This feasibility study of DiverAcción adopts a quasi-experimental pretest-posttest design without a control group, following the Medical Research Council (MRC) guidelines for complex interventions [29,30] and the SPIRIT 2025 guidelines [26]. This protocol was developed and reported in accordance with the CONSORT extension for pilot and feasibility trials, the SPIRIT 2025 guidelines for trial protocols, and the CONSORT-eHealth checklist for digital interventions [26,27,28]. This is a feasibility trial; a full protocol registration will be completed after analyzing feasibility outcomes and incorporating any necessary adaptations. The trial registry identifier will be provided once the definitive protocol is submitted. The Supplementary Material provides an integrated checklist for each guideline.

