### 2.7. Sample Size

The planned sample size is 30 children/adolescents. This number is considered adequate for feasibility and usability studies in children and adolescents [25,51], ensuring sufficient variability to identify barriers and facilitators without requiring a formal calculation of statistical power [52]. This study was designed as a pilot trial aimed at assessing the feasibility and acceptability of the intervention. The sample size (n = 30) is considered appropriate for feasibility objectives, as it allows for the evaluation of implementation aspects, adherence, usability, acceptability and participant satisfaction. However, this sample size is insufficient to establish the efficacy of the intervention; Therefore, the findings should be interpreted as preliminary and intended to inform the design of future randomized controlled trials with larger samples.

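### Repeated-measures ANOVA or Friedman drops a child who misses only T2 from the T0–T1 comparison as well; a mixed model keeps those data under a weaker missing-data assumption

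*Protocol article*

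**What the plan says.** Section 2.9.3 of the protocol article, with a qualifier that leaves room for exceptions, says that "repeated-measures ANOVA or the nonparametric Friedman test will be used to compare results at different time points". The abstract names the same two methods, with the choice depending on the data distribution. Section 2.9.3 also sets the order of reporting, "prioritizing effect sizes and confidence intervals over" p-values. The stated aim is modest: "Exploratory analyses of clinical outcomes will aim to estimate variability and preliminary trends, not to draw confirmatory conclusions". For pairwise comparisons, "Bonferroni-corrected post-hoc analyses will be performed for exploratory purposes only".

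Table 2 lists nine instruments at all three visits: BRIEF-2, TEXI, Time-S, EMT, PRMQ-C, ERQ-CA, KIDSCREEN-52, BPSES and PSI-4-SF. The rule therefore governs every repeated clinical outcome.

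On missing values, section 2.9.2 says "Sensitivity analyses using multiple imputation may be performed for exploratory clinical outcomes", and the opening of section 2.9 reserves imputation for sensitivity analyses. The complete-case sentence in 2.9.2 concerns the feasibility analyses, not the clinical outcomes. No likelihood-based method is named.

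Section 2.7: "The planned sample size is 30 children/adolescents", chosen "without requiring a formal calculation of statistical power". In Table 3, retention of at least 80% is GO and 60–79% is AMEND, while a separate row makes dropout of 30% or more STOP.

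**The concern.** In standard software both named methods need a complete T0–T1–T2 triple. T2 comes three months after the intervention ends, so some children will probably have T0 and T1 but no T2. Their observed T1 values would be left out of the main clinical analysis, including the comparison to which T2 is irrelevant.

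Two things follow. With 30 children, precision for the T0–T1 change is lost for no reason. In addition, the completers' change estimates the change in the whole group only if loss is unrelated to outcome.

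The choice also fits poorly with the plan's own priority. Friedman is a rank test and yields no mean change with an interval. At stake are the effect-size and variability estimates that section 2.7 says should inform later randomised trials.

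**Working it through.** **Inputs from the protocol article:** n = 30, one group (2.7, 2.1); visits T0, T1, T2 (2.6, Table 2); retention and dropout bands (Table 3). The sample size has no calculation behind it, so there is no planned figure to reproduce.

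**Step 1: data lost from T0–T1.** Take the most unfavourable case, in which all 30 reach T1 and all loss falls before T2. Completers n = 30 × retention. SE ratio = √(30/n). The 95% CI half-width in SDs of the change score is t(0.975, n−1)/√n. The last two columns assume loss unrelated to outcome.

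| T2 retention | Completers | Dropped from T0–T1 | SE ratio | CI half-width |
|---|---|---|---|---|
| 100% (all T0–T1 pairs used) | 30 | 0 | 1.00 | 0.37 |
| 80% | 24 | 6 | √(30/24) = 1.12 | 0.42 |
| 70% | 21 | 9 | √(30/21) = 1.20 | 0.46 |
| 60% | 18 | 12 | √(30/18) = 1.29 | 0.50 |

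The 60% line is reached only through the retention row of Table 3; the dropout row already says STOP at 30%. If some children leave before T1, fewer pairs are recoverable. With 90% at T1 and 80% at T2, the comparison is 27 pairs against 24.

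**Step 2: size of the possible bias on a raw scale.** Assumptions, none from the protocol: SD 10 at each visit, correlation 0.6, true T0–T1 change −3 (lower is better), all 30 seen at T1. The SD of the change is √(2 × 10² × (1 − 0.6)) = 8.94. The logit of T2 retention falls by a fixed slope for each point of poorer T0–T1 change. Simulated mean completer change:

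| Slope per point | 80% retention | 70% retention |
|---|---|---|
| 0 (random loss, MCAR) | −3.0 | −3.0 |
| 0.06 | −3.9 | −4.3 |
| 0.12 | −4.6 (separate runs −4.5 to −4.7) | −5.4 |

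The likelihood estimate was about −3.0 in every cell. At slope 0.12 the empirical standard error was 1.73 for completers against 1.63 at about 80% retention (6% larger), and 1.83 against 1.65 at about 70% (11% larger).

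**Step 3: does the mechanism matter?** In SD units: true change −0.50 at T1 and T2, correlation 0.5, loss at T2 only, logistic slope 1.5 per SD (again assumptions). Cells show 80% / 60% retention.

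| Loss depends on | Completers T0–T1 | Completers T0–T2 | Mixed model T0–T1 | Mixed model T0–T2 |
|---|---|---|---|---|
| Nothing (MCAR) | −0.50 / −0.50 | −0.50 / −0.50 | −0.50 / −0.50 | −0.50 / −0.50 |
| T0 value (MAR) | −0.39 / −0.29 | −0.38 / −0.29 | −0.50 / −0.50 | −0.50 / −0.50 |
| T1 value (MAR) | −0.61 / −0.71 | −0.50 / −0.50 | −0.50 / −0.50 | −0.50 / −0.50 |
| Unseen T2 value (MNAR) | −0.50 / −0.50 | −0.61 / −0.71 | −0.50 / −0.50 | −0.66 / −0.81 |

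Completer bias can run in either direction. The mixed model removes it in both MAR rows and not in the MNAR row, where its T2 estimate is slightly worse than the completers'.

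**Step 4: precision at T2.** Under MCAR at 80% retention the standard error of the T0–T2 change moves only from 0.205 to 0.199. The gain lies almost entirely in T0–T1.

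**The case against.** The strongest reply is that these analyses are exploratory, come from a "quasi-experimental pretest-posttest design without a control group", are to be read cautiously, and feed no row of Table 3. That stands, and it caps the importance of the point.

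A reader might infer that the planned methods do bias the change estimates, that completers would be the better responders, and that a mixed model cures both problems. The documents do not support this. They give no dropout mechanism. Random loss causes no bias, loss related to baseline severity makes the completers' improvement look smaller, and under MNAR the mixed model is biased too. The figures of −4.6 and −5.4 follow from a chosen dropout slope.

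A reader might also infer that Table 3 predicts loss of this size, or that the later trial will be sized on a completer SD. The bands are tolerances, not forecasts, and no passage says how that trial will be sized.

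The protocol does allow multiple imputation for these outcomes, which would use the T1 values under MAR, and it compares the baseline characteristics of completers and non-completers. These help in part. Imputation is optional and secondary, and a baseline comparison cannot reveal loss related to T1 response. Separate pairwise post-hoc tests could recover the T0–T1 pairs, and intervals could be computed apart from Friedman, but the article says neither.

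The details of missing-data handling may sit in an unseen analysis plan. The choice of method, however, is stated in the article, in both the abstract and 2.9.3.

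**Conclusion.** The point holds in limited form. As named, the methods by default exclude a child who lacks only T2 from the T0–T1 comparison: up to 6 of 30 children at the retention GO boundary and up to 9 at the dropout STOP boundary. Both counts are maxima that require all loss to fall after T1. Under random loss the T0–T1 standard error is then about 12% and 20% larger, with no bias. If loss before T2 depends on T1 response, the completer change can be biased; under the assumptions shown it lies between −3.0 and about −4.6 at 80% retention, and between −3.0 and −5.4 at 70%, against a true −3.

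A mixed model avoids discarding the T1 data and is valid under MAR with a correctly specified model, but not under MNAR. The consequence is confined to exploratory effect-size and variability estimates. It is worth correcting because the alternative is cheap and serves the plan's stated preference for estimates with intervals.

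**What to change.** In section 2.9.3, with the abstract to match:

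- For continuous scores, replace repeated-measures ANOVA with a linear mixed model for repeated measures fitted to all available T0, T1 and T2 data. Use visit as a fixed factor, an unstructured covariance with a fallback named in advance, and Satterthwaite or Kenward-Roger degrees of freedom. The MIXED procedure in the SPSS version already named can do this.
- Report mean changes T0–T1 and T0–T2 with 95% confidence intervals.
- For markedly skewed scores, give a bootstrap interval for the same model-based mean change, resampling whole children. Keep Friedman as supplementary at most.
- State that the model keeps observed T1 data from children without T2, and that it is valid under MAR but not MNAR.

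The cost is a change of wording and slightly more analysis work, with no extra data or visits. The downside is reliance on the covariance model with only 30 children, which is why the fallback should be fixed before the data are seen.
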